## Abstract

**Background:**

Rheumatoid arthritis (RA) is a chronic inflammatory disease that affects 0.5–1.0% of the population, and where many patients in spite of modern pharmacological treatment fail to reach remission. This affects physical as well as mental wellbeing and leads to severely reduced quality of life and reduced work capacity, thus yielding high individual as well as societal costs. As a complement to modern pharmacological treatment, lifestyle intervention should be evaluated as a treatment option. Scientific evidence exists for anti-inflammatory effects by single foods on RA, but no study exists where these foods have been combined to obtain maximum effect and thus offer a substantial improvement in patient life quality. The main goal of the randomized cross-over trial ADIRA (Anti-inflammatory Diet In Rheumatoid Arthritis) is to test the hypothesis that an anti-inflammatory diet intervention, compared to a regular diet, will decrease disease activity and improve quality of life in patients with stable established RA.

**Methods:**

In total, 50 RA patients with moderate disease activity are randomized to receive initially either a portfolio diet based on several food items with suggested anti-inflammatory effects or a control diet during 2 × 10 weeks with 3 months wash-out between diets. Food bags are delivered weekly by a home food delivery chain and referred to as the fiber bag and the protein bag, respectively, to partially blind participants. Both groups continue with regular pharmacological treatment. Known food biomarkers will be analyzed to measure intervention compliance. Impact on disease severity (measured by DAS28, a composite score which predicts disability and progression of RA), risk markers for cardiovascular disease and quality of life are evaluated after each diet regimen. Metabolomics will be used to evaluate the potential to predict responders to dietary treatment. A health economic evaluation is also included.

**Discussion:**

The nutritional status of patients with RA often is poor and many ask their physician for diet advice. No evidence-based dietary guidelines for patients with RA exist because of the paucity of well-conducted sufficiently large diet intervention trials. ADIRA is an efficacy study and will provide evidence as to whether dietary treatment of RA can reduce disease activity and improve quality of life as well as reduce individual and societal costs.

**Trial registration:**

ClinicalTrials.gov Registration Number: NCT02941055.

**Electronic supplementary material:**

The online version of this article (10.1186/s12937-018-0354-x) contains supplementary material, which is available to authorized users.

## Background

Rheumatoid arthritis (RA) is a chronic autoimmune disease, characterized by systemic inflammation and joint damage. In spite of modern expensive pharmacological treatment, much pain and suffering as well as reduced work capacity remain. Hence, additional treatment options such as diet interventions are requested by patients and treating physicians.

RA affects 0.5–1% of the population globally [1]. The inflammation leads to joint destruction and fatigue as well as to impaired physical functioning, work productivity and activities of daily living, and compromise overall emotional well-being. A negative impact on relationships with friends and family has been reported by one-fifth of RA patients. Further, suboptimal mental health is often reported [2]. The inflammation also leads to increased risk for cardiovascular diseases (CVD) and together with the immune-suppressive treatment also to increased risk for infections--the two leading causes of death among patients with RA [3]. Patients with RA face approximately 50% increased risk of myocardial infarction and stroke compared to the general population and their risk of CVD is comparable to that of patients with diabetes [4, 5]. Consequently, life expectancy among patients with RA is reduced by 5–10 years, compared to non-diseased individuals.

Modern RA therapy includes immunosuppression by disease modifying anti rheumatic drugs (DMARD), steroids and the more recent line of biological therapies such as TNF-α-inhibitors. The treatment aims at long-term remission i.e. no pain, tenderness of joints or functional impairment. This is achieved in 10–50% of patients with early RA [6]. However, a recent systematic review highlighted that, in spite of these modern therapies, a substantial proportion of patients with RA still experience severely impaired health [2].

Thus, in spite of modern therapy, RA continues to present a considerable human and economic burden. An estimated one-third of patients with RA terminate employment prematurely, and 5 years after diagnosis 30–40% of patients experience work disability [2]. The authors of the systematic review conclude that “*Despite advances in treatment that have helped to improve outcomes for patients with RA, treatment goals, aspirations, and expectations are seldom met for both patients and physicians. Novel treatment approaches for RA need to be tested for their ability to ameliorate contemporary unmet need.*” [2]

Associations between diet and chronic diseases such as CVD, cancer and diabetes have long been established [7, 8]. Hence, for these diseases evidence-based dietary treatment guidelines are available. In contrast, for inflammatory diseases such as RA no dietary guidelines exist, reflecting the ambiguous evidence-base. Currently, patients with RA in Sweden are encouraged to follow the same recommendations as the general population. These aim at increasing intake of fruit and vegetables to 500 g/day, fish and shellfish to 2–3 times per week, choosing whole grain over refined grain products and low-fat dairy products over full-fat varieties. Also, intake of red meat and refined sugars should be reduced [9].

The potential for diet to improve RA is obvious; diet could influence symptoms of RA by influencing the inflammatory activity, changing the lipid profile, increasing antioxidant levels, and altering the microflora of the intestine. Observational studies show lower incidences of RA among people with a healthy diet as captured by the Healthy Eating Index [10], larger consumption of LC n-3 PUFA [11] and fish [12]. Intervention studies using complete diets show that the Mediterranean diet (characterized by high intakes of olive oil and fish and low intake of red meat and dairy products), low-fat vegan diet and diets rich in unsaturated fat or probiotics have positive effects at alleviating pain and on inflammation markers [13]. Fish oil or dietary LC n-3 PUFA, i.e. reflecting fish intake, in addition to treatment with DMARD have been reported to increase the number of successful and continued DMARD treatments, indicating that pharmacological and dietary treatment complement each other [14, 15]. So far, no study has combined all components with indicative effects on RA, thus limiting the possibility to evaluate the full potential of dietary treatment of the disease. In sum, high-quality studies are needed that evaluate the combined effect of foods rich in anti-inflammatory and immune strengthening substances that could interact synergistically on RA.

Whether patients with RA respond to a dietary intervention or not might relate to genetics, habitual diet, the microbiome and/or the diversity and intensity of disease activity. Metabolomics, ie the analysis of low molecular weight metabolites, investigates overall metabolomic activity, taking genetic and environmental variation into account. It is a powerful tool to measure global and dynamic metabolic responses in disease and clinical intervention and some research also exist on RA. Different baseline metabolic profiles have been identified among patients with active RA compared to those in remission [16]. Thus, it may be possible to identify metabolic biomarkers to predict response also to dietary treatment among patients with RA. The metabolomics methods are relatively new and therefore few dietary interventions have used this approach to look at metabolic effects. Further, since the metabolism might be pertubated in patients with RA due to the metabolic syndrome or cachexia, metabolomics opens new possibilities to look at previously unknown metabolic changes as a consequence of a specific diet.

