### Research objective and specific questions

We hypothesize that an anti-inflammatory diet, in addition to pharmacological treatment, can improve health and quality of life in patients with rheumatoid arthritis. Specific questions are if an anti-inflammatory diet, compared to a usual Swedish diet, can reduce inflammation, pain and disease activity; reduce risk markers of cardiovascular disease; improve body composition; improve quality of life; reduce patient and societal costs related to the disease, and if metabolomics can be used to predict responders.

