### Participant selection

Invitation letters to the study were sent to patients with RA residing in the Västra Götaland region, Sweden, identified through the Swedish Rheumatology Quality Register, SRQ (http://srq.nu/). Responders to the invitation letters or to posters at the Sahlgrenska University Hospital were invited to screening visits. Inclusion criteria was disease duration > 2 years, active disease i.e. DAS28 ≥ 2.6 that was clinically stable and under adequate control and medication at the screening visit. DAS28 stands for Disease Activity Score, where swelling and tenderness in 28 different joints are evaluated in combination with information on erythrocyte sedimentation rate (ESR) as well as patient-reported global assessment of health [18]. Exclusion criteria included other condition demanding active medical attention, changes in DMARD during last 8 weeks, intolerant or allergic to food items included in the intervention diets or not willing to eat omnivore diet. Between February and September 2017, 13 men and 53 women, 18–70 years of age, were screened for eligibility. At the screening visit, study details were presented, informed consent obtained and habitual diet was assessed. All ADIRA study visits take place at the research ward of the Clinical Rheumatology Research Centre, Sahlgrenska University Hospital, Gothenburg, Sweden, and measurements are carried out by two registered nurses experienced in rheumatology assessments along with the project team.

Patients agreeing to participate and fulfilling all inclusion criteria were thereafter invited to baseline measurements within a few weeks. These included clinical phenotype, body composition (bioelectric impedance spectroscopy) and health assessment, 3 day food record, serum samples for blood lipids, urine sample, metabolomics and inflammation markers (e.g., high-sensitive C-reactive protein (hs-CRP), cytokines and intercellular adhesion molecules), Health Assessment Questionnaire [19] (HAQ), Quality of Life (QoL) and a questionnaire on socio-demographics, lifestyle, acute health care visits and non-steroidal anti-inflammatory drugs (NSAID) and corticosteroid consumption.

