### Metabolomics

For metabolomics, serum samples will be analyzed with nuclear magnetic resonance (NMR) at the Swedish NMR Centre at University of Gothenburg, Sweden, as well as with mass spectrometry (MS) at Chalmers Technical Institute, Gothenburg, Sweden. We will use an untargeted metabolomics approach for a global description of the metabolites that can be found in participants’ serum using unsupervised statistical analyses, ie principal component analysis (PCA). Subsequently supervised clustering, ie orthogonal projection to latent structures-discriminant analyses (OPLS-DA [25]) and OPLS-EP [26] (for paired data) will be performed to compare metabolites between patients who respond and who don’t respond to the inflammatory diet. Finally, in a targeted metabolomics approach, metabolites providing the greatest discrimination between groups of responders vs. non-responders will be identified using publicly and commercially available as well as in-house developed databases.

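### Metabolites are shortlisted as predictors of diet response on discrimination alone, with no reference to baseline DAS28, so a marker of starting disease activity could pass as a predictor

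*Protocol article*

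**What the plan says.** - **Background, metabolomics rationale.** Whether a patient responds to diet "might relate to genetics, habitual diet, the microbiome and/or the diversity and intensity of disease activity". The same paragraph reports that "Different baseline metabolic profiles have been identified among patients with active RA compared to those in remission" and infers that metabolites might predict diet response. It describes metabolomics as a tool that "investigates overall metabolomic activity, taking genetic and environmental variation into account".
- **Research objective and specific questions.** One aim is to learn "if metabolomics can be used to predict responders".
- **Metabolomics.** After PCA, OPLS-DA and OPLS-EP contrast responders with non-responders. The selection rule is that "metabolites providing the greatest discrimination between groups of responders vs. non-responders will be identified". The section names no clinical comparator and does not define response.
- **Analysis of outcome.** Adjustment for baseline disease activity and potential confounders is stated for the ANCOVA that compares outcomes between the two diets. It is not extended to the responder comparison.
- **Participant selection.** DAS28 is known at screening because it decides eligibility, and at the same visit "informed consent obtained and habitual diet was assessed".

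**The concern.** The aim is prediction, and the written rule for choosing predictors is separation of the two response groups. The Background itself expects response to vary with the intensity of disease activity, and its case for metabolomics is that metabolites track disease state. A rule that rewards separation alone can therefore rediscover baseline DAS28, which every patient already has on file.

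The problem is sharper if response means a fall in DAS28 during the diet. A patient whose baseline reading happened to be high will on average fall further, whatever the diet does. Any metabolite that moves with the baseline reading then separates the groups even if every patient has the same true benefit. It would equally appear to predict improvement on the control diet.

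At stake is how the prediction result is read, and the laboratory effort spent identifying the shortlisted compounds. The between-diet comparison of DAS28 is not at stake.

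**Working it through.** The documents give no figure for this analysis, so its size can only be illustrated.

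**1. Visit-to-visit noise, from the Sample size section.** Inputs are n = 38, difference 0.6, power 90% and α = 0.05 (two-sided assumed). The protocol article states no SD, so it has to be solved for.
- Normal approximation: SD of the paired difference = 0.6 × √38 / (1.960 + 1.282) = 1.14.
- Paired t-test (noncentral t): SD = 1.11, for which 38 patients give 90% power.

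The planned 38 can thus be matched but not confirmed. Using 1.11, the noise SD of one visit is 1.11 / √2 = 0.786.

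**2. Induced link between change and baseline.** With between-patient SD s and visit noise SD v, and the same true effect in everyone:

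corr(change, baseline) = −v / (√2 × √(s² + v²))
- s = 0.6: −0.786 / (1.414 × 0.989) = −0.56
- s = 1.0: −0.786 / (1.414 × 1.272) = −0.44

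Screening at DAS28 ≥ 2.6 narrows the spread of s a little. In simulation the correlation becomes −0.57 to −0.47.

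**3. Simulation.** There are 50 patients with screening DAS28 ≥ 2.6. Assumed inputs, not in the documents, are population mean 3.7, uniform effect 0.3, between-patient SD 0.6 to 1.0, and one metabolite correlated 0.3 to 0.5 with baseline DAS28 and otherwise unrelated to response. Responders and non-responders are compared by t-test at 0.05, then again with baseline DAS28 in the model.

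Response = DAS28 fall of at least 0.6 during the diet, unadjusted flag rate:

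| Between-patient SD | corr. 0.3 | corr. 0.4 | corr. 0.5 |
|---|---|---|---|
| 0.6 | 15% | 23% | 35% |
| 0.8 | 13% | 21% | 30% |
| 1.0 | 13% | 17% | 26% |

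Repeat runs differ by a percentage point or two, so the range is about 12% to 35%. With baseline DAS28 in the model the rate is about 5% throughout.

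**4. Other definitions of response, same set-up, unadjusted.**
- Difference between the two within-period changes: about 9% to 20%.
- End-of-diet DAS28 on one regimen against the other: about 5%, so no inflation.

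**5. Sensitivity to inputs.** A second parameterisation used n = 38 or 50, baseline SD 1.0, test–retest reliability 0.6 or 0.8, and correlations 0.3 to 0.7. It gave 8% to 40% unadjusted and 4% to 6% adjusted. The direction is stable; the size follows the assumptions.

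**The case against.** **Silence is not a decision.** The article condenses a fuller protocol, and the covariates of an exploratory metabolomics analysis are commonly left to an analysis plan. A reader might infer that the sponsor has chosen an unadjusted analysis. The text does not say so, and the lack of a covariate list is not the point. What stands is narrower: the article does state the shortlisting rule, and that rule refers to discrimination only.

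**Prediction is not causal estimation.** A metabolite that reflects disease activity, and through it true response, is a valid predictor, and the Background wants the profile to absorb several sources of variation. This is right. It rules out treating such metabolites as errors, and it argues against removing DAS28 from the metabolite data before OPLS-DA, which could delete wanted signal. It does not remove the need to show that metabolites add to a score already measured. Nor does it cover the regression-to-the-mean part, which is not response to diet at all.

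**The size depends on an assumed definition.** Response is undefined in the Metabolomics section, while the Analysis of outcome section frames the primary result as a difference between regimens. Under an end-of-diet difference with a uniform effect the inflation vanishes. This stands in full and limits the conclusion.

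**The simulation is not the planned method.** It tests one metabolite by t-test, not a multivariate OPLS model ranked by discrimination. It shows mechanism and direction only.

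**The supporting statements are indirect.** The profile difference reported in the Background is between active disease and remission, whereas this trial enrols only DAS28 ≥ 2.6. It does not establish a gradient within the enrolled range.

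**Conclusion.** The point holds in limited form and is minor. The written rule can pass off a marker of baseline DAS28 as a predictor of diet response. If response is a within-diet DAS28 fall of at least 0.6, this happens illustratively in 12% to 35% of trials for one such metabolite, against about 5% when adjusted. Those figures rest on correlations of 0.3 to 0.5, a between-patient SD of 0.6 to 1.0, a uniform true effect, and the SD of 1.11 solved from the stated sample size. If response is the end-of-diet difference between regimens and the effect is uniform, there are no excess false leads; the issue is only that value beyond DAS28 is not shown.

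Two stronger readings are not supported. A reader might infer that the inflation arises however response is defined; the end-of-diet definition shows that it does not. A reader might also count habitual diet as an equal source of false predictors. The Background links habitual diet to response but not to metabolic profile, and nothing here quantifies it. It merits a place only as a secondary covariate.

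**What to change.** In the Metabolomics section, keep the OPLS-DA/OPLS-EP comparison and add two sentences:
- Any claim that metabolites predict responders rests on improvement over a reference model of response containing baseline DAS28, with the habitual diet assessed at screening as a secondary covariate.
- The unadjusted discrimination is reported as descriptive.

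The DAS28 in the reference model should be the value from which change is counted, since its measurement error is what creates the regression to the mean. State the definition of response in the same place, because the size of the problem depends on it.

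The cost is small. The data are already collected, the model uses one or two degrees of freedom (one for DAS28, one more if habitual diet enters as a single score), and the metabolite list may become shorter.

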### Research objective and specific questions

We hypothesize that an anti-inflammatory diet, in addition to pharmacological treatment, can improve health and quality of life in patients with rheumatoid arthritis. Specific questions are if an anti-inflammatory diet, compared to a usual Swedish diet, can reduce inflammation, pain and disease activity; reduce risk markers of cardiovascular disease; improve body composition; improve quality of life; reduce patient and societal costs related to the disease, and if metabolomics can be used to predict responders.

## Methods/Design

The randomized controlled cross-over trial ADIRA (Anti-inflammatory Diet In Rheumatoid Arthritis) is carried out among patients with established RA with moderate disease activity to evaluate response to a portfolio diet treatment, compared to control diet (i.e. western diet). Both groups continue with pharmacological treatment as usual but herbal medicines or diet supplements are not allowed. In Sweden, patients with established RA are treated with DMARD and biologics at out-patient clinics according to the Swedish Society for Rheumatology Guidelines [17]. The portfolio diet treatment builds on a combination of individual food items with indicative effects on different RA symptoms. The trial thus evaluates the treatment potential of a diet based on a combination of functional concepts that likely potentiate each other in their anti-inflammatory effects. Although it is not possible to fully blind a diet intervention, the two groups are treated as similarly as possible except for diet content. Assessors of outcome are blinded. With respect to blinding of participants, see below.

The schedule of enrolment, intervention and measurements according to Standard Protocol Items: Recommendations for Intervention Trials (SPIRIT) requirements is shown in Fig. 1, and the SPIRIT Checklist is available as Additional file 1. The cross-over study is presented in Fig. 2.

**Fig. 1 Fig1:**
[figure not shown]
Content for the schedule of enrolment, intervention and measurements according to SPIRIT requirements

**Fig. 2 Fig2:**
[figure not shown]
Flow diagram of participant recruitment during the cross-over trial according to CONSORT

### Participant selection

Invitation letters to the study were sent to patients with RA residing in the Västra Götaland region, Sweden, identified through the Swedish Rheumatology Quality Register, SRQ (http://srq.nu/). Responders to the invitation letters or to posters at the Sahlgrenska University Hospital were invited to screening visits. Inclusion criteria was disease duration > 2 years, active disease i.e. DAS28 ≥ 2.6 that was clinically stable and under adequate control and medication at the screening visit. DAS28 stands for Disease Activity Score, where swelling and tenderness in 28 different joints are evaluated in combination with information on erythrocyte sedimentation rate (ESR) as well as patient-reported global assessment of health [18]. Exclusion criteria included other condition demanding active medical attention, changes in DMARD during last 8 weeks, intolerant or allergic to food items included in the intervention diets or not willing to eat omnivore diet. Between February and September 2017, 13 men and 53 women, 18–70 years of age, were screened for eligibility. At the screening visit, study details were presented, informed consent obtained and habitual diet was assessed. All ADIRA study visits take place at the research ward of the Clinical Rheumatology Research Centre, Sahlgrenska University Hospital, Gothenburg, Sweden, and measurements are carried out by two registered nurses experienced in rheumatology assessments along with the project team.

Patients agreeing to participate and fulfilling all inclusion criteria were thereafter invited to baseline measurements within a few weeks. These included clinical phenotype, body composition (bioelectric impedance spectroscopy) and health assessment, 3 day food record, serum samples for blood lipids, urine sample, metabolomics and inflammation markers (e.g., high-sensitive C-reactive protein (hs-CRP), cytokines and intercellular adhesion molecules), Health Assessment Questionnaire [19] (HAQ), Quality of Life (QoL) and a questionnaire on socio-demographics, lifestyle, acute health care visits and non-steroidal anti-inflammatory drugs (NSAID) and corticosteroid consumption.

Thereafter, patients were randomized to either diet regimen for 10 weeks. Randomization scheme was computer-generated and revealed to participants and study team at the baseline visit. At the end of the 10 wk. period, the same measurements are repeated. Individual pharmacological treatment is reported at baseline and any changes or additions in pharmacological treatment are noted during the study period. After a 2–3-mo wash-out period, the alternative diet regimen is followed for another 10 weeks. Compliance to the diets is monitored by a telephone administered interview at wk. 5 in both diet periods and with analyses of plasma phospholipid LC n-3 PUFA at the end of each diet period as well as with 3 d food record at the end of each diet period. Support for participants is provided at this telephone interview to promote trial retention; it is also possible for participants to contact the study team at any time during the intervention. Participants are asked to report any side effects. Should a participant decide to quit the trial, no further data are collected.

